### Predictor and Outcome Variables

Cardiovascular risk factors (predictor variables) used to calculate QRISK2 include age, sex, ethnicity, index of multiple deprivations, smoking status, diabetes status, family history of CVD, chronic kidney disease (stage 4 or 5), atrial fibrillation, hypertension treatment, rheumatoid arthritis, lipids, blood pressure, and BMI. EMIS will also extract prescription data. CVD outcomes will include fatal and nonfatal coronary heart disease, fatal and nonfatal stroke, heart failure, all CVD-related hospitalizations (including those for revascularization), and all-cause mortality.

### Harmonization and Cleaning of Data

Since the data for our study will be extracted at a single source (EMIS), this is likely to obviate the need for harmonizing, although we will undertake detailed quality checks (both at baseline and on follow-up) and undertake data cleaning, where necessary.

### Statistical Analyses

By using appropriate statistical tests to perform univariate comparisons, the collected data will be initially analyzed to explore the cross-sectional characteristics of this population. Skewed data will be transformed to an approximately normal distribution, with the calculation of Pearson correlation coefficients and partial correlation coefficients for relevant factors of interest.

Cross-sectional associations of baseline risk factors will be studied with adjustments for appropriate confounders using logistic regression analyses. Prospective associations between individual risk factors and CVD outcomes will be evaluated using Kaplan-Meier survival curves and further quantified by fitting Cox proportional hazards regression models with multivariable adjustments. Where possible, associations will be studied after making allowances for the time-varying effects of both exposures and potential confounders. Detailed analyses of the associations will be conducted in prespecified subgroups of participants (including, but not restricted to, age, sex, conventional risk factors, and ethnicity). Established methods of calibration (Hosmer-Lemeshow), discrimination (C or D statistic), and reclassification (net reclassification index, integrated discrimination improvement) will be used to study the predictive ability of individual risk factors on CVD outcomes, with prespecified analyses involving multiple ethnic groups to enable direct, head-to-head comparisons of any differences.

Additional analyses will be conducted to quantify the impact of factors such as access to healthcare and utilization rates (of NHS Health Checks), prescription rates and medication compliance, and patterns of healthy behavior on CVD risk (both overall and, where possible, within subgroups). Standardized rates of prescription drug use will be calculated to investigate the extent of correlation between the present use of cardiovascular medication and cardiovascular risk. Variations in prescription patterns of CVD prevention and risk factor control, discontinuation of prescribed medication(s), and adverse effects to prescription medications from various therapeutic categories such as anti-hypertensive agents, lipid-lowering drugs (statins), and antidiabetic medication will be further assessed for their impact on CVD as time-dependent covariates in Cox regression models. Physical measurements within the NHS Health Check program will be obtained by the GP practices according to standard operating procedures, anticipating minimum inter-observer variability. Analyses to explore potential sources of heterogeneity concerning physical measurements (besides other characteristics) will also be conducted.

New and existing risk prediction models will be compared in terms of their ability to predict the onset of CVD across diverse population groups to develop improved risk prediction tools for primary prevention of CVD using outcomes data up to 2020. The resulting CVD risk algorithm will be calibrated by further analyses of CVD outcomes data of these patients through to 2027.

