We developed the following study specific objectives:

To robustly quantify and characterize, across diverse ethnic groups and sociodemographic groups, the burden of CVD risk factors among NHS Health Check attendees in a diverse population in London.To prospectively study the incidence of CVD within this population by EHR linkage.To validate existing CVD risk prediction algorithms and to develop novel, bespoke algorithms for CVD risk prediction among diverse multiethnic population groups.To characterize dietary exposures and nutritional status as well as their associations with CVD outcomes, using data from index assessment methods that mirror or correlate well with those used in national surveillance.

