### Sample Size

Although data are not available for 2009-2011, of the invited population for NHS Health Check in 2016-17, 51.6% and 49.9% were residing in London and the rest of England, respectively [27]. In 2015, EMIS utilization in GP clinics was approximately 55%. Therefore, if 50% of all NHS Health Check attendees visit GP clinics utilizing the EMIS system, then it can be assumed that 587,273 individuals in London are eligible for consideration in this study between 2011 and 2017 [28,29]. Due to a lack of visibility of the true number of GP practices using a particular system, Figure 2 highlights that the majority of the areas in London do utilize the EMIS system, and, therefore, we anticipate that the intended sample size will be met.

To develop novel risk prediction tools for population groups, we anticipate that data will be available on approximately 200,000 individuals across London between 2011 and 2017. During 2009-13, of those with a recorded ethnic group, uptake of the NHS Health Check across England was greatest amongst South Asians (19.2%), Black Caribbeans (19.6%), Black Africans (15.7%), and Chinese (15.3%). Attendance was 16.9% in all other recorded ethnic groups and 17.4% in white Caucasians. Extrapolating the current rate of CVD incidence (2.4%) for people aged below 79 years in England on our estimated study sample of 200,000, we expect to encounter 15,000 CVD events giving 100% power to observe relative risks as modest as 1.2-1.5 [23]. Within population subgroups, the power to detect overall association is expected to range from 49% to 100% [38,39]. Given the large Black and minority ethnic (BME) population in London and considering the above numbers, we estimate that our study sample will be highly representative of a diverse cohort [38,39].

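### Logistic regression is the only adjusted cross-sectional regression named, so BP, lipids and BMI would have to be cut at a threshold whenever they are the outcome; a linear model should be added

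*Protocol article*

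**What the plan says.** The first study-specific objective, listed at the end of the Introduction, is "To robustly quantify and characterize, across diverse ethnic groups and sociodemographic groups, the burden of CVD risk factors among NHS Health Check attendees". Predictor and Outcome Variables lists the factors concerned. Many are binary or categorical, such as smoking status and atrial fibrillation, but the list ends with "hypertension treatment, rheumatoid arthritis, lipids, blood pressure, and BMI", and the last three of these are measured on a continuous scale.

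Statistical Analyses sets out three cross-sectional steps:

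- Unadjusted description: "By using appropriate statistical tests to perform univariate comparisons, the collected data will be initially analyzed to explore the cross-sectional characteristics".
- Full-scale correlation: "Skewed data will be transformed to an approximately normal distribution, with the calculation of Pearson correlation coefficients and partial correlation coefficients".
- Adjusted modelling: "Cross-sectional associations of baseline risk factors will be studied with adjustments for appropriate confounders using logistic regression analyses".

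The third step covers baseline risk factors without distinction and names one model. It states neither the dependent variable nor any cut-point. Later in the same section, further analyses of heterogeneity in physical measurements are promised, with no model named.

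**The concern.** When burden is compared across ethnic or deprivation groups, the risk factor is naturally the outcome and the group is the exposure. Ordinary binary logistic regression can take blood pressure, lipids or BMI as an outcome only after a cut. Adjusted ethnic differences would then appear as odds ratios for exceeding a threshold, and shifts elsewhere in the distribution would be lost.

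The continuous factors carry much of this objective. According to the Introduction's section on the population prevention strategy, people with existing CVD, diabetes or hypertension are not invited, so those diagnoses should be uncommon at baseline.

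The section also sits awkwardly with itself. Its second step takes care to put skewed variables on a usable continuous scale, and its third step names a model that does not use that scale for an outcome.

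**Working it through.** **1. Is there a figure in the plan to reproduce?** No. The only power statement, in Sample Size, is based on expected CVD events and relative risks. Nothing is given on the precision of cross-sectional comparisons or on cut-points.

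**2. Do the other named methods give adjusted group differences on the full scale?**

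- Univariate comparisons use the full scale but are not adjusted.
- Partial correlations use the full scale and are adjusted. They return a unitless coefficient, not an adjusted difference in mmHg, mmol/L or kg/m² between ethnic groups.
- The heterogeneity analyses name no model.
- Entering a continuous factor as a covariate in a logistic model keeps its scale, but does not estimate its level by ethnic group.

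**3. Information lost if a normal variable is cut.** For a shift in the mean, with share p above the cut c, the asymptotic relative efficiency is

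ARE = φ(c)² / [p(1 − p)], where φ is the standard normal density.

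| Share above cut (assumed) | φ(c) | ARE | Loss |
|---|---|---|---|
| 50% | 0.3989 | 0.1592/0.2500 = 0.637 | 36% |
| 25% | 0.3178 | 0.1010/0.1875 = 0.539 | 46% |
| 15% | 0.2332 | 0.0544/0.1275 = 0.426 | 57% |
| 10% | 0.1755 | 0.0308/0.0900 = 0.342 | 66% |
| 5% | 0.1031 | 0.0106/0.0475 = 0.224 | 78% |

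Normality and equal SDs are assumed. Group size does not enter the formula, so the proportional loss is the same for large and small groups.

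**4. Simulation check.** With 2,000 against 20,000 people, a shift of 0.08 SD, 1,500 runs, and a mean-difference z compared with a log odds ratio Wald z, relative efficiency was 0.64 at the median cut and 0.38 at the 10% cut. The second is a little above the asymptotic 0.34, since the shift is not infinitesimal. Power fell from 92% to 77% and from 93% to 56%.

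**5. Practical size.** The plan gives no ethnic group sizes. Assume a reference group of 118,000, which is 59% of 200,000, applying the Discussion's 41% BME share of London's population to the sample. The smallest difference detectable with 80% power (two-sided 5%) is (1.960 + 0.842) × √(1/n + 1/118,000) SD for the linear analysis. Dividing by √ARE gives the value after a cut.

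| Group size n (assumed) | Linear | Median cut | 10% above cut |
|---|---|---|---|
| 1,000 | 0.089 SD | 0.112 SD | 0.152 SD |
| 2,000 | 0.063 SD | 0.079 SD | 0.108 SD |
| 4,000 | 0.045 SD | 0.056 SD | 0.077 SD |
| 10,000 | 0.029 SD | 0.037 SD | 0.050 SD |

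With an assumed systolic SD of 16 mmHg, the first row is 1.4, 1.8 and 2.4 mmHg and the last row 0.5, 0.6 and 0.8 mmHg.

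**6. Power for one small difference.** Take 1 mmHg (d = 1/16 = 0.0625 SD) and a cut with 25% of the reference group above it; the shifted group then has 27.03% above. For n = 2,000 the linear z is 0.0625/√(1/2,000 + 1/118,000) = 2.77, or 79% power. The difference in proportions gives z = 2.03, or 53%. The same calculation gives 50% against 30% for n = 1,000, 97% against 81% for n = 4,000, and over 99% on both scales for n = 10,000.

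**The case against.** The strongest reply is that dichotomisation is nowhere stated. A reader might infer that the plan commits to cutting blood pressure, lipids and BMI. It does not: the dependent variable is unstated, these measures are introduced as predictors, and the preceding step keeps them continuous. That stands, and is why the point is conditional on the sentence being followed as written with these measures as outcomes.

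Second, partial correlation is an adjusted full-scale method. With a 0/1 indicator for an ethnic group and the other covariates partialled out, its test is equivalent to that of the linear regression coefficient, and deprivation is ordered in any case. This also stands, so an adjusted full-scale test could be obtained from the named methods. It would still not report the size of a group difference in usable units.

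Third, prevalence above a recognised threshold is a proper measure of burden. The Introduction speaks of prevalence of hypertension and diabetes, and the Discussion plans population attributable risk. Where prevalence is the target, the binary outcome is the estimand and no information about it is wasted. The efficiency figures apply only to the question of a shift in the mean.

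Fourth, the sample is large. A 41% BME share of 200,000 is 82,000 people. Over four to eight groups that averages about 20,500 to 10,250 each, where the loss hardly affects power for the example above.

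Finally, an article condenses its full protocol, and the model for each factor may be set there. But the article does more than stay silent: it assigns all adjusted cross-sectional associations to one named model.

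**Conclusion.** The point holds as a cheap improvement to a stated model choice. It is not an error that threatens the study. Logistic regression is the only adjusted cross-sectional regression named. It fits the binary factors and threshold prevalence, but it is not the best tool for adjusted group differences in blood pressure, lipids and BMI.

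The loss of about 36% to 66% applies to a normal variable cut with between 50% and 10% of people above. The plan supplies neither cuts nor group sizes, so this is an illustration and not a property of the plan.

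Two further inferences are tempting and should not be drawn:

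- The loss is not proportionally greater in small groups. It is the same everywhere, and only its practical consequence is confined to groups of a few thousand or fewer.
- The lower figure in "Within population subgroups, the power to detect overall association is expected to range from 49% to 100" per cent is not a benchmark for these comparisons. It follows directly on the statement about CVD events and relative risks, and so concerns associations with CVD outcomes.

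**What to change.** In Statistical Analyses, add multivariable linear regression as the adjusted cross-sectional analysis for systolic and diastolic blood pressure, lipids and BMI, using the transformation already planned where a variable is skewed. Report adjusted mean differences, or ratios for log-transformed variables, by ethnicity and deprivation. Restrict the logistic regression sentence to binary factors and to the prevalence of exceeding recognised thresholds, and state those thresholds.

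The cost is a change of wording and one further set of regressions on data already extracted. The downside is two sets of estimates for each continuous factor, a mean or ratio difference and a prevalence, which lengthens the reporting.

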### Population Prevention Strategy in England

In England, the National Health Service (NHS) established a population-based Health Check program in 2009 to provide a systematic assessment and management of CVD risk for adults. Individuals aged 40-74 years without pre-existing CVD, diabetes, or hypertension are invited for a five-yearly check-up to identify and to receive advice and treatment for their risk of having a CVD event [6]. Commissioned by local authorities and delivered primarily through primary care practices, henceforth referred to as general practices (GP), this program aims to prevent around 2000 deaths and 9500 nonfatal myocardial infarctions (MI) and strokes annually [7,8]. As a free service for all eligible individuals, this program has the potential to reduce health inequalities associated with CVD [7,8], assuming equitable uptake and universal coverage. Available data suggest that between 2011-12, NHS Health Check coverage in east London was quite high at 73% (compared to national coverage of 30%). Of those that attended the screening, over a third belonged to ethnic minority groups such as south Asians and Black African/Caribbeans [9-13]. While modification of individual risk factors (eg, blood pressure) has generally been shown to be associated with improved health outcomes (eg, lower incidence of ischaemic stroke), favorable changes in risk factor distribution at a societal level have also contributed to overall improvements in community health [14]. For example, in 1989, in Poland, the increased accessibility and consumption of fruits and vegetables through the opening of markets resulted in a reduction in CVD mortality [15]. By contrast, Japanese migrants, who adopted the diet and lifestyle of the United States (US) population, relative to those who retained their original dietary patterns, had a higher prevalence of CVD [16]. Given the variation in ethnic-specific diet and lifestyle habits, and given genetic differences across population groups around the world, there is currently an unmet need to understand the complex relationship between ethnicity and factors as diverse as heredity, environment, diet, lifestyle, and socioeconomic factors (and their mutual interaction) in determining the burden, distribution, and temporal trends in both CVD risk factors and clinical CVD outcomes and cause-specific death.

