### Data Collection and Linkage

Our study, designed as a population-based registry at the outset, will collect, alongside NHS Health Check data, additional demographic variables and prescription information to help build a large and robust repository of primary care data on residents of London undergoing NHS Health Check from 2009 onwards in GP practices.

All individuals seeking healthcare in the United Kingdom are assigned a unique identifier (ie, their NHS number). This number allows the allocation of any subsequent data collected to the individual’s record and enables linkage with diverse data sources. For instance, the Office for National Statistics and Hospital Episode Statistics databases maintain records on mortality and clinical outcomes of individuals utilizing secondary healthcare services, respectively. Data from these sources can be linked through NHS numbers to the NHS Health Check data to provide a comprehensive and contemporary database on CVD risk factors (predictor variables) and outcomes across different ethnic groups. Other data sources recording clinical CVD outcomes such as the Myocardial Infarction National Audit Project and the National Institute of Cardiovascular Outcomes Research will also be harnessed to provide additional details relevant to this study.

This process of data sharing and linking, while protecting an individual’s confidentiality, is possible due to pseudonymization and will be conducted by EMIS and a third party organization familiar with bespoke linkage. Using Open Pseudonymiser Software, EMIS will create a pseudonymized version of NHS numbers for individuals who meet the inclusion criteria. The data will be encrypted with a project-specific key. By using this encrypted key, an external organization will be able to link the NHS Health Check data with outcomes data through a similar pseudonymization process and a Global Unique Identifier (GUID). The research team will only have access to completely linked anonymized data as the linkage of NHS Health Check data with outcomes data will not contain the GUID.

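### Time-dependent Cox models for prescribing and discontinuation do not, as described, estimate impact on CVD, because blood pressure and lipids both prompt treatment and are changed by it

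*Protocol article*

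**What the plan says.** In the protocol article, the second part of Statistical Analyses begins: "Additional analyses will be conducted to quantify the impact of factors such as access to healthcare and utilization rates". Prescription rates and medication compliance are among the factors listed there. It then names the exposures, "Variations in prescription patterns of CVD prevention and risk factor control, discontinuation of prescribed medication(s), and adverse effects to prescription medications", and the drug classes, "anti-hypertensive agents, lipid-lowering drugs (statins), and antidiabetic medication". These "will be further assessed for their impact on CVD as time-dependent covariates in Cox regression models". No other method is named for drug effects.

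Three other statements bear on the point:

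- **Why treatment starts.** Population Prevention Strategy in England says that eligible people are invited every five years "to identify and to receive advice and treatment for their risk of having a CVD event".
- **The safeguard.** Earlier in Statistical Analyses, after a mention of multivariable adjustment: "Where possible, associations will be studied after making allowances for the time-varying effects of both exposures and potential confounders". No technique is given.
- **The data.** Data Collection and Linkage says the study "will collect, alongside NHS Health Check data, additional demographic variables and prescription information". Results says that extraction and linkage were complete by March 2020.

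**The concern.** The article fixes both a target (the effect of prescribing and stopping on CVD) and a model (Cox regression with time-dependent covariates). The model does not suit the target.

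Starting an antihypertensive or a statin depends on measured risk, and the drug then lowers blood pressure or lipids. If the current value is left out, treated people look worse because they were at higher risk. If it is put in, the model holds fixed the route by which the drug works. Adjusting for baseline alone leaves the confounding that builds up after baseline.

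Discontinuation has a separate problem. If some prescriptions end because the patient is already becoming ill, a covariate that switches at the stop date assigns the following event to stopping.

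At stake is whether effective preventive drugs look ineffective and stopping looks more harmful than it is. These analyses are wanted within subgroups where possible. Where prescribing or stopping differs between ethnic groups, the bias would differ too and could pass for an ethnic difference. A large cohort makes such an estimate more precise, not less biased.

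**Working it through.** The article states no figure for these effects, so there is nothing to reproduce. The drug effect, strength of indication and frequency of illness-driven stopping are not in the document. All are assumptions.

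**Drug use, true ratio 0.75.** The simulations use yearly intervals; A, B and C were fitted by pooled logistic regression, the discrete-time form of a time-dependent Cox model.

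- A: 200,000 people, 7 years, start odds ×2.7 per SD of the risk factor, drug lowers it by 0.6 SD, 10% stop per year.
- B: 40,000 people, 10 years, no stopping. The drug acts only by lowering the factor by 0.5 SD, and event log-odds rise 0.6 per SD, so the conditional odds ratio is exp(−0.6 × 0.5) = 0.74. The always-versus-never-treated ratio in the simulated data is 0.75.
- C: 100,000 people, 10 years. The drug acts directly, not through the factor. Stopping depends on a persisting illness.
- D: 60,000 people, 7 intervals, start odds ×1.3 to ×2.7 per SD, with 0% to 100% of the effect through the factor.

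| Scenario | Unadjusted | Baseline-adjusted | Current-value-adjusted |
|---|---|---|---|
| A | 1.46 | 1.01 | 1.04 |
| B, no indication | 0.74 | 0.73 | 0.98 |
| B, start log-odds 1.5 per SD | 1.95 | 1.12 | 1.02 |
| C, no indication | 0.78 | 0.78 | 0.77 |
| C, start log-odds 0.5 / 1.0 / 1.5 per SD | 1.12 / 1.26 / 1.26 | 0.85 / 0.81 / 0.77 | 0.76 / 0.73 / 0.75 (illness also adjusted) |
| D | not reported | 0.73 to 0.86 | 0.99 to 1.00 (all effect through the factor) |

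Three things follow.

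1. When the drug acts through the risk factor, adjusting for the current value removes the effect (0.98 to 1.04), even with no indication. Using the value measured before that year's treatment decision does little better: 0.92 in B without indication and 0.95 with it.
2. Baseline-adjusted results run from 0.73 to 1.12, so they can be nearly right or badly wrong.
3. In B with strong indication, a stabilised inverse-probability-weighted marginal structural model returns 0.75. It does so because every confounder is measured in the simulation.

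**Stopping, true ratio 1.** Assume a constant hazard, stopping at 8% a year and 6 years of follow-up.

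- Time on drug: (1 − exp(−0.08 × 6))/0.08 = (1 − 0.619)/0.08 = 4.76 years
- Time off drug: 6 − 4.76 = 1.24 years
- Ratio of on to off: 3.86 (from unrounded values)

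If a fraction f of on-drug events is preceded by an illness-driven stop, those events move to off-drug time. The on-drug rate is multiplied by (1 − f) and the off-drug rate by (1 + 3.86f), so the apparent ratio is (1 + 3.86f)/(1 − f).

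- f = 0.10: 1.386/0.90 = 1.54
- f = 0.20: 1.772/0.80 = 2.21 (2.215 before rounding down)
- f = 0.30: 2.158/0.70 = 3.08

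Simulation C gives the same direction when stopping is truly harmful (1/0.75 = 1.33). As illness-driven stopping strengthens, the unadjusted ratio is 1.62, 1.95 and 2.11. With baseline risk it is 1.61, 1.83 and 1.96. With current risk and illness fully measured it is 1.43, 1.37 and 1.31.

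**The case against.** The strongest reply is that the plan already allows for time-varying confounders, that a journal article need not spell out weights and lags, and that a marginal structural Cox model is itself a Cox model with time-dependent treatment. The planned text therefore does not rule out the right analysis. That is true, but the allowance is conditional and names no technique. Its most natural reading, updated values entered in the same regression, is the version that removes the drug effect.

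Further parts of the reply stand:

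- **Size.** It rests on assumptions. If the drug did not act through the measured confounders and all were captured, ordinary adjustment would largely suffice (0.73 to 0.76 in C with indication present). The unadjusted reversals (1.46, 1.95) come from a model the article does not clearly propose.
- **Stopping.** A reader might infer that discontinuation estimates can also vanish or reverse. The calculations show exaggerated harm instead. That stopping follows illness is plausible but stated nowhere in the article.
- **One joint model.** A reader might infer that prescribing, discontinuation, adverse effects and risk-factor control enter together. The text speaks of models in the plural, and risk-factor control can be read as the purpose of the prescribing, not as a separate covariate. Treatment starts are likewise inferred from prescription patterns.
- **Data.** Weighting needs repeat measurements. Checks are five-yearly, and the article does not say whether interim values were extracted.

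**Conclusion.** The concern holds in a limited form. For drugs that act through blood pressure or lipids, the described model cannot be relied on to estimate impact on CVD, and the article's general allowance for time-varying confounding does not resolve this. Under assumed inputs with a true ratio of 0.75, adjusting for the current value gives about 1.0 when the drug works through that factor, and adjusting for baseline gives about 0.73 to 1.12. The harm of stopping is exaggerated to about 1.5 to 3.1 against 1 if 10% to 30% of on-drug events follow an illness-driven stop.

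That treatment follows measured risk rests on the article; the sizes and the illness-driven stopping are assumptions. A reader might infer that the study's main results are compromised. The document does not support that: these are labelled additional analyses, no listed objective is a drug effect, and the burden, incidence and prediction objectives are not directly affected. The point should be corrected before drug-effect results are reported.

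**What to change.** Amend the sentence on medication analyses in Statistical Analyses as follows.

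1. Lag discontinuation: count a stop as exposure only after, for example, 6 months, with 3 and 12 months as sensitivity analyses. A lag deals with stops in the run-up to an event. It does not remove confounding by an illness that persists, which is why diagnoses belong in step 2.
2. Where time-updated blood pressure, lipids and diagnoses are already in the extract, estimate drug effects with a marginal structural Cox model using inverse-probability-of-treatment weights, and do not condition on post-treatment values.
3. Otherwise keep the lag, report these models as descriptive associations, and replace the word *impact* with *association*.

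The cost is plan wording, some extra analysis and slightly wider intervals. No new extraction is needed. That matters because extraction and linkage are complete and the researchers hold anonymised data without the linkage identifier, so adding variables could mean repeating both steps. If repeat values are not held, step 3 is the realistic route.
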